## Abstract

**Background:**

The latest global figures show that 55 million persons lived with major neurocognitive disorders (MNCDs) worldwide in 2021. In Quebec, Canada, most of these older adults are cared for by family physicians in interdisciplinary primary care clinics such as family medicine groups (FMG). When a person has a MNCD, taking potentially inappropriate medications or polypharmacy (5 different medications or more) increases their vulnerability to serious adverse events. With the recent arrival of pharmacists working in FMGs and their expanded scope of practice and autonomy, new possibilities for optimizing older adults’ pharmacotherapy are opening.

**Objective:**

This project aims to evaluate the impact of involving these pharmacists in the care trajectory of older adults living with MNCD, in an interdisciplinary collaboration with the FMG team, as well as home care nurses and physicians. Pharmacists will provide medication reviews, interventions, and recommendations to improve the pharmacotherapy and support offered to these patients and their caregivers.

**Methods:**

This 2-step mixed methods study will include a quasi-experimental controlled trial (step 1) and semistructured interviews (step 2). Older adults undergoing cognitive assessment, recently diagnosed with MNCD, or receiving care for this at home will be identified and recruited in FMGs in 2 Quebec regions. FMGs implementing the intervention will involve pharmacists in these patients’ care trajectory. Training and regular mentoring will be offered to these FMGs, especially to pharmacists. In control FMGs, no FMG pharmacist will be involved with these patients, and usual care will be provided.

**Results:**

Medication use (including appropriateness) and burden, satisfaction of care received, and quality of life will be assessed at study beginning and after 6 months of follow-up and compared between groups. At the end of the intervention study, we will conduct semistructured interviews with FMG care team members (pharmacists, nurses, and physicians) who have experienced the intervention. We will ask about the feasibility of integrating the intervention into practice and their satisfaction with and their perception of the intervention’s impacts for older adults and their families. We will assess the effect of improved pharmaceutical care for older adults with or at risk of MNCDs through the involvement of FMG pharmacists and a reorganization of pharmaceutical care.

**Conclusions:**

The inclusion of pharmacists in interdisciplinary care teams is recent and rising, strengthened by more substantial pharmacist practice roles. Results will inform the processes required to successfully involve pharmacists and implement developed tools and procedures transposable to other care settings to improve patient care.

**Trial Registration:**

ClinicalTrials.gov NCT04889794; https://clinicaltrials.gov/ct2/show/NCT04889794

**International Registered Report Identifier (IRRID):**

DERR1-10.2196/42577

## Introduction

The latest global figures show that 55 million persons lived with major neurocognitive disorders (MNCDs) in 2021, and this number is expected to rise to 78 million in 2030 and 139 million in 2050 [1]. Older adults with MNCDs are more likely to be exposed to polypharmacy or potentially inappropriate medications than those without this condition [2]. Polypharmacy, the simultaneous use of 5 or more different medications, increases older adults’ vulnerability to falls, emergency department visits, hospitalizations [3], and loss of autonomy [4]. For example, adverse effects of medications can be a precipitating factor in delirium [5]. In turn, delirium increases the risk of prolonged hospitalization and functional decline and doubles the mortality rate [6]. Better pharmacotherapy management for vulnerable older adults may prevent this iatrogenic chain leading to autonomy loss. According to several recent studies and literature reviews, interdisciplinary interventions that include pharmaceutical care and knowledge exchange sessions with health care teams can reduce inappropriate medication [7,8] or prevent the onset of delirium for at-risk individuals [9].

Since October 2015, the Quebec Ministry of Health and Social Services has provided resources to integrate pharmacists into interdisciplinary family medicine group (FMG) teams to improve medication use [10]. These pharmacists are working in the clinic, together with other health care professionals, in the provision of direct patient care. As of April 2021, 328 (88.6%) of the 370 FMGs had an agreement in place with 1 or more pharmacists, according to the Ministry. The pharmacist presence in the FMG was a mean of 16.3 and 19.1 hours per week in 2018 and 2020, respectively [11,12]. In January 2021, their role was further expanded by increased practice rights [13]. Notably, pharmacists can now initiate or modify a pharmacotherapy independently under certain conditions and, even more liberally, within a collaborative practice agreement with physicians [13].

Pharmacists are the health care professionals best trained to identify inappropriate medications [14], thus improving prescribing, reducing evitable health care utilization and medication costs, and contributing to the clinical improvement of many health conditions [14-16] and patients’ experience [17], specifically when part of the health care teams. Additionally, FMG pharmacists are particularly well positioned to review and optimize medications for patients undergoing cognitive assessment who frequently have inappropriate medication therapy [18]. A prior study examined this new model of functioning for pharmaceutical care in FMG among persons with complex care needs [19]. According to this study, the mean number of medications prescribed per person was 14.2, and FMG pharmacists identified an average of 7.2 problems related to pharmacotherapy during their evaluation and follow-up of 4 to 6 months [19]. A prior study in Quebec long-term care facilities on the increased role of pharmacists practicing in these settings demonstrated that it was possible to reorganize care, based on expanded pharmacists’ and nurses’ scope of practice, to reduce polypharmacy and inappropriate medications in older adults in long-term care [20]. Collaboration and work satisfaction among health care providers also improved [21,22].

Presently, not all FMGs have a pharmacist in their team, and when present, the FMG pharmacist is not always involved in the care trajectory of older adults with MNCDs. This study, therefore, aims to involve FMG pharmacists systematically in the care of these patients, a role which has been encouraged by the Quebec Alzheimer Plan [23,24]. This study will assess whether pharmacists’ systematic involvement in these patients’ care, together with their increased practice roles, can reduce treatment burden, polypharmacy, or potentially inappropriate medications and improve patients’ care, their satisfaction with care, and quality of life. We developed the intervention, called GPS (Évaluation de l’impact de la réorganisation du travail en GMF sur la pharmacothérapie et le soutien à l’autonomie des personnes âgées ayant un trouble neuro-cognitif majeur) together with the stakeholders of the Quebec Alzheimer Plan. Patient partners have also been involved in the study from its beginning and helped develop all recruitment and interviewing material. The intervention’s goal is to reduce the number of adverse effects due to inappropriate pharmacotherapy and its consequences on functional decline and loss of autonomy in older adults with MNCDs. We hypothesize that the intervention will decrease (1) the number of prescribed medications, (2) the proportion of patients with potentially inappropriate medication, and (3) patients’ perceived treatment burden and increase (4) patients’ satisfaction with care and (5) their quality of life.

## Methods

### Study Design

We based our methodology on the Medical Research Council's conceptual model on how to evaluate complex interventions [25]. We will use mixed methods, including a quasi-experimental controlled trial (step 1) and semistructured interviews (step 2). For step 1, information on health conditions and medication utilization at study entry and follow-up (ie, after 6 months) will be collected for all included participants. Participating patients will also complete 3 validated questionnaires in either French or English to assess their perceived treatment burden, quality of life, and satisfaction with care. The Multimorbidity Treatment Burden Questionnaire, (MTBQ) [26,27], the EQ-5D-5L [28], and the self-administered Physician Enabling Skill Questionnaire (PESQ) [29] will be used. Pharmacists will also report their interventions and suggestions during the 6-month follow-up. In step 2, we will invite all health professionals who implemented the intervention (ie, pharmacists, nurses, and physicians) to participate in a semistructured interview where they will be asked about the ease to integrate the intervention into their practice, their satisfaction with it, and their perception of its impacts for older adults and their families.

### The GPS intervention

First, nurses and physicians in intervention FMGs (exposed) will be asked to refer all older adults undergoing cognitive evaluation OR referred to a memory clinic OR recently diagnosed (<12 months) with a MNCD to the FMG pharmacist. Moreover, home care teams will be asked to refer older adults receiving home care for MNCDs to the FMG pharmacist. FMG pharmacists will perform a medication review. A medication review is a structured and comprehensive evaluation of a patient’s pharmacotherapy with the aim of identifying and resolving problems and improving health outcomes [30]. This medication review involves an interview with each referred older adult, including their caregiver, if applicable, to establish the best possible medication history (BPMH) [31]. The BPMH is a complete documentation of medication therapy, including the name, dose, administration route, and medication administration frequency. To this end, medication information will be validated with at least 1 other reliable data source (eg, community pharmacy records) and documented in the patient’s chart. The pharmacist will then detect medication-related problems [32] by analyzing this information and clinical data using their own judgment or validated criteria [33]. They will establish a care plan and the follow-ups needed with the patient in collaboration with the health care team and the community pharmacist. Pharmacists will also document the number and type of interventions and recommendations made to optimize patients’ pharmacotherapy for 6 months following the medication review. We will offer training and mentoring support to these teams, including pharmacist support for more complex interventions and monthly web-based interdisciplinary meetings.

### Study Setting

The study will comprise participants from an exposed group of approximately 5 FMGs with attending pharmacists who will implement the intervention and a control group composed of participants from 5 others FMGs without involved pharmacists. FMGs and home care teams will participate at their convenience within 2 Integrated (University) Health and Social Services Centers territories: (1) the *Centre intégré universitaire de santé et de services sociaux* (CIUSSS) *du Nord-de-l’Ile-de-Montréal* (NIM) in a metropolitan area and (2) the *Centre intégré de santé et de services sociaux* (CISSS) *de Chaudière-Appalaches* (CA) in a mixed—urban and rural—area. We used this selection process to facilitate implementation as the intervention teams need to be motivated toward its application and training and mentoring activities. To be eligible for participation, intervention FMGs must have at least 1 participating pharmacist, interested partner nurses, and physicians. Similarly, intervention home care teams must have access to a participating FMG pharmacist and a home care nurse. In contrast, in control FMGs and their home care teams, no FMG pharmacist will be systematically involved in the eligible patients’ trajectory. However, the FMGs must be willing to allow data collection and delay implementing similar interventions within their teams.

### Study Population

For the first step, the intervention targets 2 patient subgroups at turning points: (1) older adults undergoing cognitive evaluation or recently diagnosed with MNCDs in FMGs and (2) older adults with MNCDs followed at home by the home care teams.

For the second step, FMG professionals and home care teams implementing the intervention are also targeted.

#### Step 1: Quasi-experimental Controlled Trial

##### Inclusion and Exclusion Criteria for Older Adults

All older adults (aged ≥65 years) undergoing cognitive evaluation at the FMG OR referred to a memory clinic OR having been diagnosed with MNCDs at the FMG within the last year OR followed up at home for a MNCD AND referred to the pharmacist in the intervention FMGs will be invited. We will exclude older adults in palliative care or those who do not understand French or English (without a caregiver who could assist them).

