##### Sample Size Calculation

According to prior estimates provided by the CI(U)SSS, about 50 older adults may be targeted for participation per FMG per year. Considering that the on-site presence of FMG pharmacists is on average 2 to 3 days a week [11,12], it should be feasible to include approximately 40 older adults per FMG. By setting our intercluster correlation coefficient at 0.005 (conservative), the number of clusters (FMGs) at 5 intervention and 5 control FMGs, and at 40 older adults per FMG, we expect to be able to detect a difference of 1 medication per older adults between the beginning and the end of the intervention, between the 2 groups, with a power of 83%. Therefore, we have planned a 12-month inclusion period, corresponding to recruiting approximately 1 person per week per FMG. The inclusion date will be when the reference to the pharmacist was made. For control FMGs, we will consult electronic medical records and FMG health care professionals to identify all older adults who meet the inclusion criteria. Since there will be no reference to the pharmacist for these individuals, the inclusion date will be the date of identification by the FMG. For those receiving home care services, the inclusion date will be the first home visit following the start of the study.

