### Data Analysis

In step 1, we will use an intention-to-treat approach to assess the GPS intervention’s effectiveness. The principal analysis will compare the difference (1) in the average number of medications per person between the unexposed and exposed groups according to the study period (baseline and 6 months) and (2) the average number of potentially inappropriate medications per person between the 2 groups, according to the study period, by mixed Poisson repeated measures regression. This type of analysis considers intra-FMG and intraindividual correlations. Contrasts will be built to determine if the average number of medications per person over time differs between the exposed and the unexposed group. Secondary results will be analyzed similarly to compare the MTBQ, PESQ, and EQ-5D-5L scores between the groups exposed and unexposed to the GPS intervention.

Medication data missing at measurement time periods after the initial data collection will be imputed using the last-observation-carried-forward method. Using this method, the potential benefits of the intervention should be underestimated. For participants lost to follow-up regarding the questionnaires, no measures will be imputed at follow-up, but sensitivity analyses may be used in which baseline questionnaires scores could be imputed for follow-up scores. We will perform all analyses with SAS statistical software (SAS Institute Inc).

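### Intervention patients enter only once referred to the pharmacist, controls on eligibility alone: one arm is conditioned on uptake, and the intention-to-treat label does not hold at FMG level

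*Protocol article*

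**What the plan says.** **Entry.** In the protocol article, *Inclusion and Exclusion Criteria for Older Adults* lists the qualifying routes and ends with patients "OR followed up at home for a MNCD AND referred to the pharmacist in the intervention FMGs will be invited". For control FMGs, *Sample Size Calculation* says "we will consult electronic medical records and FMG health care professionals to identify all older adults who meet the inclusion criteria".

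**Inclusion date.** The same section gives three rules. The general rule is "The inclusion date will be when the reference to the pharmacist was made". For control FMGs: "Since there will be no reference to the pharmacist for these individuals, the inclusion date will be the date of identification by the FMG". For home care, with no group named: "For those receiving home care services, the inclusion date will be the first home visit following the start of the study".

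**Role of referral.** *The GPS intervention* opens with referral as the first component: "nurses and physicians in intervention FMGs (exposed) will be asked to refer all older adults undergoing cognitive evaluation", as well as those sent to a memory clinic or recently diagnosed. Home care teams are asked to refer their patients too.

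**Exposure and analysis.** *Sampling Method, Recruitment, and Data Collection Procedure* defines the group by whether the patient's FMG has a participating pharmacist. *Data Analysis* states "we will use an intention-to-treat approach to assess the GPS" intervention, with a contrast of change in mean medication count between the two groups.

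**The concern.** Exposure is a property of the FMG, but in intervention FMGs a patient enters the study only after the first step of the intervention has already happened. Control patients pass no such filter. An eligible patient in an intervention FMG whom nobody refers is absent from the data, while the counterpart in a control FMG is sought out.

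An FMG-level intention-to-treat comparison asks what happens to all eligible patients when their FMG adopts the programme. As written, the comparison sets referred patients against eligible patients.

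What is at stake is the primary outcome. If referral is incomplete and related to medication count, regression to the mean can produce a change in one arm only, and the group-by-time contrast would read it as an effect of the intervention. A larger sample would not remove this.

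**Working it through.** **1. The rules side by side**

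| | Intervention FMGs | Control FMGs |
|---|---|---|
| Entry | eligible and referred | eligible, found through records and professionals |
| Inclusion date | referral | identification by the FMG |
| Home care date | referral or first home visit: both rules can apply | first home visit |
| Eligible, unreferred | not entered | no such category |

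The string of ORs and one AND in the eligibility sentence could be read as tying referral to the home care route only. The inclusion-date rules point the other way: the general date is the referral, and control FMGs get a different date precisely because they have no referral.

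**2. The plan's power figure**

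Inputs from *Sample Size Calculation*: 5 + 5 FMGs, 40 patients each, intracluster correlation 0.005, difference 1 medication, power 83%. The article gives no SD or alpha, so the 83% cannot be reproduced directly. Assuming two-sided alpha 0.05:

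- Design effect = 1 + (40 − 1) × 0.005 = 1.195.
- Effective n = 200 / 1.195 = 167.4 per group.
- The SD of change that gives 83% is 3.14.

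This SD is used only in step 5. The selection point does not depend on it.

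**3. How many could be left out**

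The article expects about 50 eligible patients per FMG per year and plans about 40, citing pharmacist presence: 40 / 50 = 80%. That leaves 10 per FMG, or 50 over five intervention FMGs. Treating 80% as the referral fraction is my assumption; the article calls it feasible inclusion.

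**4. Ceiling on regression to the mean**

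Assume normally distributed counts and the extreme case of referral strictly from the highest count downwards. With fraction f referred:

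- Shift in SD units = φ(z) / f, where z cuts off the lowest 1 − f. At f = 0.8 this is 0.280 / 0.8 = 0.35.
- Spurious fall = (1 − r) × shift × SD, where r is the baseline to 6-month correlation.

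With SD 5 (assumed):

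| f | Shift (SD) | r = 0.9 | r = 0.8 |
|---|---|---|---|
| 1.0 | 0 | 0 | 0 |
| 0.8 | 0.35 | 0.175 (about 0.18) | 0.35 |
| 0.7 | 0.50 | 0.25 | 0.50 |
| 0.5 | 0.80 | 0.40 | 0.80 |

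At f = 0.8, widening the assumptions to SD 3 to 5 and r 0.7 to 0.9 gives 0.10 to 0.52. Selection on a trait only correlated with the count gives less. If simpler cases are referred first, the sign reverses.

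**5. What analysing all eligible patients would cost**

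Assume no effect in unreferred patients. At 80% referral the FMG-level effect is 0.8 × 1 = 0.8 medication. With SD 3.14:

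- 200 per group (effective 167.4): power about 65%.
- 250 per group (design effect 1 + 49 × 0.005 = 1.245, effective 200.8): power about 72%.

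**The case against.** The strongest reply is that clinicians are asked to refer every eligible patient, on cognitive status and not on medication count. If they do, the two entry rules coincide and there is no selection. This stands as a limit on the size of the problem. It does not remove it: the article describes no search for unreferred patients in intervention FMGs, and its own planning figure falls short of everyone.

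Other replies also stand. Control patients are found partly through professionals, so their ascertainment may be selective too. A difference in baseline level does not by itself create a difference in change. Referred patients who never receive a review can still be analysed as exposed, so the departure lies in who enters, not in how enrolled patients are grouped.

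A reader might go further in four ways that the article does not support:

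- **Referral picks patients with long medication lists and so manufactures most of the 1-medication difference.** Nothing in the article shows selection by count. A shift of 0.5 to 1 SD would need referral of only about the top 70% to 38%, against a planned 80%.
- **Baseline means must differ systematically.** They may or may not; the direction is unknown.
- **Referral was very low, because 100 participants were enrolled by September 2022.** Against 11 × 50 = 550 eligible patients in a full year, that is at most about 18%. But enrolment also reflects consent and the pandemic-related delays in deployment and recruitment that the *Discussion* reports, so it is not a referral rate.
- **A home-visit inclusion date that precedes pharmacist contact is an error.** A baseline before contact is acceptable. The problem is only that two dating rules can apply to the same patient.

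**Conclusion.** The asymmetry is explicit in the text: entry and time zero depend on referral in one group and on identification in the other. Because referral is part of the intervention and exposure is set by the FMG, the intention-to-treat label does not hold at FMG level. That conclusion needs no assumed figure.

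The size of any bias does rest on assumptions. It is zero with complete referral. At the planned 80% it is at most about 0.18 to 0.35 medication, that is 18% to 35% of the target difference, under normality, SD 5, r of 0.8 to 0.9 and strict selection by highest count. It could be larger if referral is lower, and its direction cannot be settled from the article. Separately, the inclusion date for intervention home care patients is ambiguous.

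**What to change.** **Preferred change**

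- Run the record-and-professional search planned for control FMGs in intervention FMGs as well, and apply one inclusion-date rule to both groups.
- For the medication outcomes, make the primary comparison by FMG group in all eligible consenting patients, referred or not. Keep the referred-only comparison as secondary.
- State which inclusion date applies to home care patients in intervention FMGs.
- Report the numbers eligible, referred and enrolled for each FMG.

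This is feasible because the search is already planned for controls, medication outcomes come from medical records and can be re-dated, and control FMGs were still being recruited.

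**Cost.** A protocol amendment; a search in the intervention FMGs; approaching and consenting unreferred patients; and dilution of the effect if referral is incomplete (illustrative power about 65% to 72% at 80% referral, against the stated 83%). Questionnaires already completed cannot be re-dated, so the change is cleanest for the chart-based outcomes.

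**If this is not adopted.** Restate the target as the effect among referred patients, drop the intention-to-treat label, and adjust for baseline medication count and case mix. This costs little, but the adjustment deals only with measured differences.
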